### 7.2 Sample Size Considerations

- Dengue surveillance in San Pablo City over the past 4 years has demonstrated annual incidence rates of infant hospitalized dengue between 0.05-0.25%. The

population of infants between 0-16 months of age in San Pablo City is approximately 16,000-20,000. A study cohort continuously maintained at 4,000 subjects in this age range will capture infant hospitalized dengue rates of 0.1-0.2% with 90% confidence (EpiInfo, [www.cdc.gov/epiinfo](http://www.cdc.gov/epiinfo)).

- To identify subjects with mild/asymptomatic dengue, we will measure asymptomatic seroconversion in a subset of 250 subjects/year. We anticipate a 1-3% yearly incidence of mild/asymptomatic dengue [12]. A sample of 250 subjects will capture a mild/asymptomatic dengue incidence rate of 1-3% with 90-95% confidence (EpiInfo, [www.cdc.gov/epiinfo](http://www.cdc.gov/epiinfo)).
- Based on these sample sizes and assumptions, we anticipate capturing the following number of subjects over a 4-year period:

| Hosp DHF | Hosp DF | Non-hosp DF | Mild/asymptomatic seroconversion
(from random sample of $n=250/\text{year}$ ) |
|----------|---------|-------------|----------------------------------------------------------------------------------|
| 11       | 11      | 44          | 32                                                                               |

At the end of the study period, we expect to have nearly  $n=100$  infants with DV infections, and a much larger pool without evidence of DV infections to select matched controls ( $n=200$  or  $300$ ). Data analysis with these anticipated numbers is detailed in section 7.4.

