### **Objectives:**

#### Primary:

- Define the levels of serotype-specific neutralizing antibody (Ab) associated with protective immunity against symptomatic dengue.

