### 7.4 Analysis Plan

I. ***First study objective- correlate pre-existing, maternally-derived, neutralizing Ab titers against the infecting DV serotype with disease severity.***

Subjects with hospitalized DHF will be rated as severity=5, and each step downward in severity category will be rated by a decrease in one point on a severity scale (4, 3, etc.). Neutralizing Ab titers determined in the pre-infection blood draws, and predicted neutralizing Ab titers at the time of illness based on a kinetic model of anti-DV Ab clearance (see below), will be used for analysis. The association between pre-existing neutralizing Ab titers (raw and log-transformed) and severity of DV infections will be evaluated by fitting partial proportional odds multivariate longitudinal models [28, 29]. When needed, we will also use generalized estimating equations [30, 31], clustering on patient observations over time, while using a logit link function and unstructured error correlation structure. Analyses will be performed separately

for each DV serotype, as well as with all serotypes pooled (and serotype included as a candidate term in the model).

We will also compare pre-existing, maternally-derived, neutralizing Ab titers against the infecting DV serotype to peak viremia levels measured in subjects with symptomatic dengue. In this subset, we will fit a multiple linear regression model for peak viremia with neutralizing Ab titer levels, and other potential covariates. Model selection will be by partial F-tests [32] on the difference in residual error.

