The kinetics of serotype-specific anti-DV neutralizing Abs will be characterized in Filipino infants from 6-14 weeks to 16 months. We will do this using a two stage approach [33]. Serial plasma samples from 30 study subjects who did not have evidence of a DV infection from birth to 16 months, and born to DV-immune mothers (neutralizing Ab titers to  $\geq 2$  DV serotypes), will be collected. In the first stage, the elimination half lives ( $t_{1/2\beta}$ ) of neutralizing Abs to DVs 1-4 will be estimated from the slopes of linear fits to the log Ab titer concentrations over time for each subject. In the second stage, the serotype-specific  $t_{1/2\beta}$ 's will be fitted in linear regression models which will include Ab levels to the other serotypes and other covariates, i.e. factors which might impact maternal Ab decline or otherwise predict Ab levels. The significance of covariates will be assessed using F tests [32]. Model adjusted (least squares or estimated population marginal means [34]) estimates of these parameters with their standard errors will be generated. We will estimate the pre-existing anti-DV neutralizing Ab titers at the time of illness in symptomatic dengue cases using the previously constructed model. Neutralizing Ab titers will be estimated at which 25%, 50% and 75% of the subjects developed a symptomatic DV infection.

**II. Second study objective- measure the strength of association of anti-DV Ab effects (neutralization or enhancement) with development of DHF, controlling for other potential covariates.**

The variables that will be examined as potential covariates were selected to represent different aspects of the infant host response to primary DV infection, and are summarized in the table in Section 7.1. Using the pre-infection samples, potential risk and protective factors will be evaluated in multiple logistic regression analyses. Infants who develop hospitalized DHF will be the disease group (i.e. event), and the other subjects whose disease severity decreases at least one category on the disease severity scale will serve as controls. Models will be constructed in a stepwise manner using likelihood ratio chi-squared statistics to evaluate improvement in fit [35].

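### The serotype-specific objective rests on sparse separate fits, or on a pooled model that may drop serotype; the pooled model with serotype fixed should be the main analysis

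*Protocol*

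**What the plan says.** The Protocol Summary states the primary objective: "Define the levels of serotype-specific neutralizing antibody (Ab) associated with protective immunity against symptomatic dengue". Section 2.1 adds the hypothesis that protective levels are not the same for all serotypes.

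Section 7.2 starts from surveillance showing "annual incidence rates of infant hospitalized dengue between 0.05-0.25"% and a "population of infants between 0-16 months of age in San Pablo City is approximately 16,000-20,000". It then says "A study cohort continuously maintained at 4,000 subjects in this age range will capture infant hospitalized dengue rates of 0.1-0.2% with 90% confidence", and makes a similar statement for 250 infants a year (mild or asymptomatic incidence 1-3%, confidence 90-95%). It tabulates the expected four-year yield as 11 hospitalized DHF, 11 hospitalized DF, 44 non-hospitalized DF and 32 mild/asymptomatic, and closes with "Data analysis with these anticipated numbers is detailed in section 7.4".

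Section 7.4, first study objective, specifies partial proportional odds models of severity on pre-existing titre, run separately "for each DV serotype, as well as with all serotypes pooled (and serotype included as a candidate term in the model"). It also says "Neutralizing Ab titers will be estimated at which 25%, 50% and 75% of the subjects developed a symptomatic DV infection".

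Section 4 (Outcomes) finds Categories I-III by surveillance of the enrolled cohort. Category IV (mild/asymptomatic) is found only among the 250 infants a year selected for Study Visit 3.

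**The concern.** The size calculation contains no titre, severity scale or serotype, yet its yield is passed straight to the titre-severity models. Two routes then lead to a serotype-specific answer. Four separate fits share 98 infections between them. The pooled fit has enough information on titre, but whether serotype stays in it is left to selection. If serotype drops out, the better-informed model gives a single protective titre, and the serotype-specific result rests on the weakest fits in the plan.

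A second problem arises when any such model is used for the titres at 25, 50 and 75% symptomatic infection. The ratio of 66 symptomatic to 32 mild infections partly reflects how many infants are sampled for mild infection, so it is not the ratio in the cohort.

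**Working it through.** **1. The plan's own figures.** The protocol names EpiInfo but not the formula or all inputs, so this is an inference from reproduction. One-sample survey size: n0 = z²p(1−p)/d², with finite-population correction n = n0/(1 + n0/N).
- Expected 0.2%, worst acceptable 0.1% (d = 0.001), 90% confidence: n0 = 5,400. With N = 16,000, n = 4,038; with N = 20,000, n = 4,252. The planned cohort is 4,000.
- Expected 3%, worst acceptable 1% (d = 0.02): 197 at 90% and 279 at 95% confidence. The planned 250 lies between them.

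Both figures behave as precision sizes for a rate.

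**2. Infections per serotype.** 11 + 11 + 44 + 32 = 98. An even split gives 98/4 = 24.5 infections and 11/4 = 2.75 DHF cases per serotype. The protocol gives no serotype mix. The chance that at least one serotype has no DHF case, by inclusion-exclusion:
- even split: 4(0.75)¹¹ − 6(0.5)¹¹ + 4(0.25)¹¹ = 17%;
- assumed 50/25/15/10 split: 47%.

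**3. Power for the titre slope.** The protocol states no effect, so odds ratios (OR) per SD of log titre are assumed, with two-sided alpha 0.05. For a proportional odds model the information is n·f, where f = (1 − Σp³)/3. With p = (11, 11, 44, 32)/98, Σp³ = 0.128 and f = 0.2906. Power = Φ(ln OR·√(n·f) − 1.96).

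| Infections | Power, OR 1.5 | Power, OR 2 | Power, OR 3 | Detectable OR at 80% power |
|---|---|---|---|---|
| 98 (pooled) | 58% | 96% | >99% | 1.69 |
| 49 (half share) | 33% | 74% | 99% | 2.10 |
| 24.5 (even split) | 19% | 46% | 83% | 2.86 |
| 10 | 10% | 22% | 47% | 5.17 |

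Simulated ordinal fits (200 runs per setting) agreed at OR 2: 94% at n = 98, 44% at 25 and 28% at 10. These use one common slope. The partial proportional odds model may add slopes by severity cut, which asks more of the same data.

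**4. Chance that selection drops serotype.** Assume a 5% test on 3 degrees of freedom, serotype independent of titre, and protective titres that differ between serotypes with standard deviation s (in SD of log titre). The noncentrality is λ = 98 × 0.2906 × (s·ln OR)².
- OR 2: s = 0.25 gives λ = 0.86, dropped in 90%; s = 0.5 gives λ = 3.42, dropped in 69%; s = 1 gives λ = 13.68, dropped in 11%.
- OR 3: s = 0.25 gives λ = 2.15, dropped in 80%; s = 0.5 gives λ = 8.59, dropped in 31%.

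So moderate real differences can easily be lost; large ones would usually be kept.

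**5. Sampling of mild infections.** If a fraction π of mild infections is sampled and all symptomatic ones are, the odds of symptomatic infection in an unweighted model are inflated by 1/π. The estimated 50% titre then moves by ln(1/π)/ln OR, towards too high a titre when antibody protects. Assume π = 10% (4 × 250 = 1,000 of 10,000 infants): ln 10/ln 2 = 3.3 SD at OR 2, and ln 10/ln 3 = 2.1 SD at OR 3. At π = 250/4,000 the shifts are 4.0 and 2.5 SD.

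**6. The 98 may be generous.** 32 seroconversions from 4 × 250 = 1,000 infants is 3.2%, above the stated 1-3% (10-30 infants). In the Section 4 outcome table, positive IgM alone establishes infection in Categories I-III but serotype comes from RT-PCR, so an IgM-only case cannot enter a serotype-specific fit.

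**The case against.** The strongest reply is that the protocol plans the pooled fit too, and that fit has good power. This stands. A reader might infer that 98 infections cannot support the primary analysis at all. The documents do not show that: they give neither an effect size nor a serotype mix, and the table shows 83% power at OR 3 with an even split and a detectable OR of 2.1 for a serotype with half the infections. Outright failure is also not the rule: in simulation the DHF cut could not be estimated in 5-12% of fits at n = 25, rising to 41-50% at n = 10.

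A reader might also take the 90% figures as a claim of power. Section 7.2 makes no such claim, and a missing power statement may be dealt with in an analysis plan not seen here. The point therefore does not rest on it. It rests on what Section 7.4 does fix: separate fits by serotype, and serotype as an optional term in the pooled model.

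Section 7.2 mentions 200 or 300 matched controls, which might seem to enlarge the analysis. However, Section 6.2.1 plans neutralizing titres for Categories I-IV only, and an uninfected infant has no infecting serotype against which to read a titre.

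Finally, the sentence on 25, 50 and 75% titres names no model and follows the estimation of titres in symptomatic cases, so it could mean quantiles among cases. The weighting advice is conditional for that reason. It would be wrong to infer from the protocol how often intervals for those titres would be unbounded.

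**Conclusion.** The point holds as one of method. The sizes in Section 7.2 address incidence, and at the anticipated yield the separate serotype fits are sparse: about 46% power at OR 2 with 24.5 infections and 22% with 10. They detect only large effects unless one serotype dominates. The pooled fit is adequate for the titre slope (96% at OR 2), but leaving serotype to selection puts the serotype-specific objective at risk. Serotype would be dropped in roughly 70-90% of studies at OR 2 if protective titres differ by 0.25-0.5 SD, and in about 11% if they differ by 1 SD.

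These figures assume 98 infections with known serotype, the stated severity split, a common slope and a 5% selection test; Section 7.4 states no selection rule for this model. They do not show that the study fails. They show that the better-informed model should be specified so that it answers the stated question.

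**What to change.** In Section 7.4, first study objective:
- Make the pooled model the main analysis, with titre against the infecting serotype and serotype as a fixed term that is never removed by selection.
- Check a titre-by-serotype interaction, and label the four separate fits descriptive.
- Where this model is used for the titres at 25, 50 and 75% symptomatic infection, weight each mild/asymptomatic infection by the inverse of its sampling fraction (the 250 selected that year over the infants eligible for selection), with standard errors that allow for the weights. Say which infants the weighted estimate describes.

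The cost is wording and modest analysis work. The model carries three extra parameters and assumes similar slopes across serotypes, which the interaction check examines, though with limited power. Weighting widens the intervals for the 25, 50 and 75% titres and requires the yearly count of eligible infants to be kept.

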### 7.3 Participant Enrollment and Follow-Up

After start-up, enrollment and subject accrual will occur on a continuous, rolling, basis in order to maintain the cohort goal of 4,000 infants between the ages of 6 weeks to 16 months. New infants between the ages of 6-14 weeks will be enrolled to replace those disenrolled after reaching age 16 months. There is no additional follow-up for subjects after leaving the study at age 16 months.

### 7.4 Analysis Plan

I. ***First study objective- correlate pre-existing, maternally-derived, neutralizing Ab titers against the infecting DV serotype with disease severity.***

Subjects with hospitalized DHF will be rated as severity=5, and each step downward in severity category will be rated by a decrease in one point on a severity scale (4, 3, etc.). Neutralizing Ab titers determined in the pre-infection blood draws, and predicted neutralizing Ab titers at the time of illness based on a kinetic model of anti-DV Ab clearance (see below), will be used for analysis. The association between pre-existing neutralizing Ab titers (raw and log-transformed) and severity of DV infections will be evaluated by fitting partial proportional odds multivariate longitudinal models [28, 29]. When needed, we will also use generalized estimating equations [30, 31], clustering on patient observations over time, while using a logit link function and unstructured error correlation structure. Analyses will be performed separately

for each DV serotype, as well as with all serotypes pooled (and serotype included as a candidate term in the model).

We will also compare pre-existing, maternally-derived, neutralizing Ab titers against the infecting DV serotype to peak viremia levels measured in subjects with symptomatic dengue. In this subset, we will fit a multiple linear regression model for peak viremia with neutralizing Ab titer levels, and other potential covariates. Model selection will be by partial F-tests [32] on the difference in residual error.

The kinetics of serotype-specific anti-DV neutralizing Abs will be characterized in Filipino infants from 6-14 weeks to 16 months. We will do this using a two stage approach [33]. Serial plasma samples from 30 study subjects who did not have evidence of a DV infection from birth to 16 months, and born to DV-immune mothers (neutralizing Ab titers to  $\geq 2$  DV serotypes), will be collected. In the first stage, the elimination half lives ( $t_{1/2\beta}$ ) of neutralizing Abs to DVs 1-4 will be estimated from the slopes of linear fits to the log Ab titer concentrations over time for each subject. In the second stage, the serotype-specific  $t_{1/2\beta}$ 's will be fitted in linear regression models which will include Ab levels to the other serotypes and other covariates, i.e. factors which might impact maternal Ab decline or otherwise predict Ab levels. The significance of covariates will be assessed using F tests [32]. Model adjusted (least squares or estimated population marginal means [34]) estimates of these parameters with their standard errors will be generated. We will estimate the pre-existing anti-DV neutralizing Ab titers at the time of illness in symptomatic dengue cases using the previously constructed model. Neutralizing Ab titers will be estimated at which 25%, 50% and 75% of the subjects developed a symptomatic DV infection.

**II. Second study objective- measure the strength of association of anti-DV Ab effects (neutralization or enhancement) with development of DHF, controlling for other potential covariates.**

The variables that will be examined as potential covariates were selected to represent different aspects of the infant host response to primary DV infection, and are summarized in the table in Section 7.1. Using the pre-infection samples, potential risk and protective factors will be evaluated in multiple logistic regression analyses. Infants who develop hospitalized DHF will be the disease group (i.e. event), and the other subjects whose disease severity decreases at least one category on the disease severity scale will serve as controls. Models will be constructed in a stepwise manner using likelihood ratio chi-squared statistics to evaluate improvement in fit [35].

Adequacy of the fit for the final model will be evaluated using the Hosmer-Lemeshow Goodness of Fit Test [36]. Point and interval estimates of relative risk will be made by exponentiating model coefficients and their 95% confidence intervals [35]. Analyses will be performed with all DV serotypes pooled, and as serotype included as a candidate term in the model.

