**Neutralizing Ab assays-** All subjects in the clinical study with evidence of DV infection (Categories I-IV) will have neutralizing anti-DV Ab titers determined in their pre-infection blood draw. The neutralizing Ab titers will be determined using a standard plaque reduction assay to reference DV isolates serotypes 1-4 [13]. We have previously shown that neutralizing Ab titers to reference DV isolates correlate well with neutralizing Ab titers to the actual infecting virus isolate [13]. The 50% plaque reduction neutralization titer will be calculated using 4-parameter curve fitting analysis.

**Peak viremia determinations-** We have found that viremia levels obtained within 72 hours of symptom onset in dengue are a good approximation of peak viremia levels [20-22]. A serotype specific, fluorogenic, quantitative RT-PCR assay will be performed on the acute illness serum samples collected within 72 hours of symptom onset from infants in Categories I-III.

**Ab-dependent enhancement of infection assay (ADE)-** All subjects in the clinical study with evidence of DV infection or likely exposure (Categories I-IV) will have an ADE Ab assay performed using their pre-infection blood draw.

**PBMC activation-** We recognize that limited numbers of PBMC will be available for study from the infant blood draws. Therefore, we plan to use modern multiplex assay techniques to get an overview of DV-induced immune activation patterns in infant PBMC. We will first perform the assays on serial collected PBMC (study visits 1 and 2) from 30 subjects without evidence of DV infection (Category V). This will allow us to refine the assays. Once optimized, the assays will be done on the pre-infection PBMC from all subjects with evidence of DV infection (Categories I-IV).

PBMC will be stimulated in vitro with DV and controls. At the early and late time points, cell culture supernatants will be collected and cellular RNA will be isolated. Pro- and anti-inflammatory cytokine/chemokine levels will be determined in the supernatants using a multiplex bead assay. 9 cytokines/chemokines will be assayed in a single sample using the preconfigured panel shown below:

| Category                    | Mediators                                                      |
|-----------------------------|----------------------------------------------------------------|
| Pro-inflammatory mediators  | IL-1 $\beta$ , IL-6, TNF- $\alpha$ , IFN- $\gamma$ , IL-12 p70 |

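### Infecting serotype is not fixed in the peak-viremia regression: at most it is a candidate term that a partial F-test can remove, which can bias the pooled titre slope

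*Protocol*

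**What the plan says.** Peak viremia is the secondary outcome (Protocol sections 4 IV and 7.1), and the primary objective in section 3 relates titre to it.

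- **Outcome.** Section 6.2.1: "A serotype specific, fluorogenic, quantitative RT-PCR assay will be performed on the acute illness serum samples collected within 72 hours of symptom onset". It covers clinical categories I-III.
- **Predictor.** Titres are measured "using a standard plaque reduction assay to reference DV isolates serotypes 1-4" (section 6.2.1). The comparison in section 7.4 I uses "neutralizing Ab titers against the infecting DV serotype to peak viremia levels measured in subjects with symptomatic dengue", so the reference strain behind the titre changes with the infecting serotype.
- **Model.** Section 7.4 I specifies a "multiple linear regression model for peak viremia with neutralizing Ab titer levels, and other potential covariates. Model selection will be by partial F-tests". Titre is the only named term. The study-variables table in section 7.1 does not list infecting serotype.
- **Serotype elsewhere.** The severity paragraph, immediately before the viremia paragraph, ends by planning analyses "for each DV serotype, as well as with all serotypes pooled (and serotype included as a candidate term in the model". For the DHF models in 7.4 II: "Analyses will be performed with all DV serotypes pooled, and as serotype included as a candidate term in the model". The viremia paragraph has no such sentence.

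**The concern.** The question is whether, among infants infected with the same serotype, a higher pre-existing titre goes with lower peak viremia. A slope fitted across serotypes without a serotype term also picks up differences between serotype averages. If serotypes differ on average in both viremia and titre, a slope appears even when antibody does nothing. Depending on the direction of the gaps, a real slope may instead be hidden.

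A selection rule based on significance is a weak safeguard here. In a few dozen infants a real serotype difference will often be non-significant, and the term is then removed although it still confounds the slope. The secondary-outcome result would then depend partly on which serotypes circulated. The protocol itself hypothesises in section 2.1 that protective titres differ by serotype.

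**Working it through.** **1. Number of infants.** The section 7.2 table gives 11 + 11 + 44 + 32 = 98 infections, which reproduces the stated total of nearly 100. The viremia model uses only the symptomatic cases: 11 + 11 + 44 = 66, or 66/4 = 16.5 per serotype if evenly spread. The 72-hour sampling limit lowers this further. If about 60% qualify (an assumption), 0.6 × 66 ≈ 40. The protocol states no alpha, power or effect size for this regression, so there is no planned figure to reproduce.

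**2. Bias if serotype is out of the model.** With a true slope of zero, the pooled slope tends to

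between-serotype covariance of titre and viremia ÷ (within-serotype + between-serotype variance of titre).

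Assume two equally common serotypes, a within-serotype SD of 1.0 log10 for viremia and 0.5 log10 for titre, and the higher-titre serotype having the lower viremia. With gaps dV and dT this is −(dV·dT/4) ÷ (0.25 + dT²/4).

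- dV = 0.5, dT = 0.3: −0.0375 / 0.2725 = −0.14.
- dV = 1.0, dT = 0.5: −0.125 / 0.3125 = −0.40.

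So the slope is −0.14 to −0.40 log10 viremia per log10 titre when the truth is 0. With the gaps in the same direction the sign reverses.

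**3. False-positive rate.** Simulation used the same assumptions, n = 40 and 66, 2,500-3,000 runs per setting and two-sided 0.05 (assumed). Three rules were compared: serotype omitted; serotype kept only if its partial F-test has p < 0.05; serotype always in. The partial F for k serotypes is

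[(RSS without serotype − RSS with) / (k − 1)] ÷ [RSS with / (n − k − 1)].

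| Assumed setting | Omitted | F-test selection | Always in |
|---|---|---|---|
| Two serotypes, gaps 0.5-1.0 (viremia) and 0.3-0.5 (titre) | 7-37% | 6-11% | 4-6% |
| Four serotypes (50/30/15/5%), between-serotype SD 0.5-1.0 and 0.3-0.5 | 8-33% | 7-9% | 5-6% |
| Small differences, SD 0.25 and 0.15 | 5-6% | 5-6% | 5-6% |

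Ranges span repeated runs. In the two-serotype setting the F-test kept serotype in only about 29-96% of runs.

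**4. A second set of assumptions.** Four serotypes, equally common or 10/20/30/40%, with 4,000 runs per setting. With a top-to-bottom gap of one within-serotype SD in both variables, F-test selection gave 9.0-10.2% across n = 33, 44 and 66, against 5.0-5.6% with serotype always in. With gaps up to 2 SD, selection ranged over 5-10% at n = 66 and 8-20% at n = 33. With no serotype differences all three rules stayed near 5%.

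**5. Retention threshold.** The protocol gives none. In the two-serotype settings, selection at 0.05 gave 6.0-10.5%, at 0.10 gave 5.6-9.0% and at 0.20 gave 5.1-7.7%; always in gave 4.0-5.7%.

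**6. Cost of always including serotype.** The standard error rises by 0-8% in one set of runs and up to about 11% in another. If serotype does not matter and the true slope is −0.35 SD per SD, power falls from 78.3% to 76.3% (n = 66), 59.6% to 56.0% (n = 44) and 48.5% to 45.0% (n = 33), a loss of 2.0, 3.6 and 3.5 points.

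**The case against.** Four arguments on the other side carry weight.

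- **The severity sentence may cover viremia.** It stands under the same objective, uses the same predictor, and the viremia paragraph follows at once. On that reading, separate fits by serotype are already planned. A reader might infer that the protocol definitely pools viremia and ignores serotype; the text does not establish that. What survives is that, even on the generous reading, serotype in the pooled model is a removable candidate, and about 16 infants per serotype or fewer make the separate fits weak on their own.
- **The largest error rates describe an analysis that is not clearly planned.** The 7-37% applies only if serotype is never offered to the model. This stands: the relevant comparison is 6-11% against about 5%.
- **The assays may share a common scale.** A reader might infer from the serotype-specific RT-PCR that four assays are calibrated differently. The protocol says nothing of the kind. The point does not need it: any average difference between serotypes in both variables, whatever its source, is enough.
- **Covariate lists belong in the analysis plan.** Often so. But this protocol states the selection rule, and that rule allows a likely confounder to be dropped. Replacing a stated rule is a fair protocol comment.

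It is also true that a single serotype-adjusted slope assumes the same slope in every serotype. That is a reason to keep the separate fits alongside it.

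**Conclusion.** The point holds, with moderate size. Section 7.4 I does not secure infecting serotype in the viremia model on either reading. Under the assumed gaps (0.5-1.0 log10 in viremia, 0.3-0.5 log10 in titre), F-test selection gives a false-positive rate of about 6-11% where about 5% is intended.

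This rests on gaps, SDs, a serotype mix and a retention threshold that the protocol does not give. Both variables must differ by serotype for any bias to arise. Small gaps make the problem negligible, a looser threshold shrinks it, and wider gaps with fewer infants enlarge it. The change should be made because it is cheap and needs no new data, with medium confidence in how much it matters.

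**What to change.** In section 7.4 I, state that:

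- any pooled peak-viremia model always contains infecting serotype as a fixed factor, exempt from partial F-test selection;
- the serotype-adjusted titre slope is the reported result;
- partial F-tests apply only to the remaining covariates;
- the separate fits by serotype also apply to viremia where numbers allow.

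No extra data are needed, because serotype is determined from RT-PCR (section 4 IV) and a serotype-specific viremia value comes with a known serotype.

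The cost is a short addition to the text, up to 3 degrees of freedom, a standard error up to about 11% larger, and about 2-4 points of power if serotype turns out not to matter.
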